## List of Abbreviations

|       |                                         |
|-------|-----------------------------------------|
| AOWCL | Acute Old World cutaneous leishmaniasis |
| CL    | Cutaneous leishmaniasis                 |
| CR    | Case Report Form                        |
| i.l.  | Intralesional                           |
| MA    | Meglumine antimoniate                   |

## Summary

Cutaneous leishmaniasis is a major health problem in many developing countries and affects hundreds of thousands of people each year. It is associated with a high disease burden at both individual and social levels in endemic areas. Looking for simple, inexpensive treatment methods is continued.

Unfortunately the conventional treatments of cutaneous leishmaniasis tend to concentrate only on the treatment of the microbial cause of this disease and little attention have been paid to other aspects of wound management in this disease.

This study is designed to assess of the efficacy of a combination of intralesional injections of meglumine antimoniate and non-silver dressing or silver dressing in comparison with the intralesional injections of meglumine antimoniate in the treatment of cutaneous leishmaniasis due to *L. major* through conducting a randomized ,assessor-blind controlled clinical trial.

## Aim and objectives

**Primary objective:** To compare the proportion of cured patients between treatment group treated with intralesional injections of meglumine antimoniate MA and non-silver dressing and treatment group treated with intralesional injections of meglumine antimoniate 10 and 14 weeks of follow-up.

To compare the proportion of cured patients between treatment group treated with intralesional injections of meglumine antimoniate and silver dressing and treatment group treated with intralesional injections of meglumine antimoniate 10 and 14 weeks of follow-up.

## **Secondary objectives**

To compare: 1) the proportion of relapsed patients 6 months after initiation of treatment, 2,) the mean time to heal of the lesions and, 3) the proportion of adverse effects during the study period in three groups.

To answer: 1) Is the combination of intralesional injections of meglumine antimoniate and non-silver dressing more effective than the intralesional injections of meglumine antimoniate in the treatment of CL due to *L. major*?, and 2) is the combination of intralesional injections of meglumine antimoniate and silver dressing more effective than the intralesional injections of meglumine antimoniate in the treatment of CL due to *L. major*?

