## **Secondary objectives**

### **To compare:**

- the proportion of relapsed patients 6 months after initiation of treatment
- the proportion of adverse effects during the study period in three groups

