**Sample size**

Fifty-six lesions per treatment group were needed to have 80% power to detect a significant difference in the expected cure rate of 60% in the i.l MA alone group and the desired cure rate of 85% in the i.l. MA and either silver or non-silver dressing-treated group at week 10 with a type I error level of 0.05. Compensating for a 20% loss-to-follow up, recruiting 68 (round up to 70) lesions per treatment group will be reasonable.

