**Outcome measures**

The primary end point of this study is the clinical cure of the lesion (complete healing is defined as more than 75% reduction , clinical improvement defined as 50%-75% reduction, and no response to treatment defined as less than 50% reduction in the size of the lesion compared with baseline). The end-points will be assessed at the end of the treatment period (end of week 6) and 4 weeks later.

The secondary end-points include treatment related side effects and relapse. The relapse is defined as a reappearance of lesions at the site or periphery of previously healed lesions or an increase in the size of lesions after initial improvement was assessed 5 months after the termination of treatment.

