**Statistical methods**

The recorded data will be entered in SPSS 17 for Windows software (SPSS Inc, Chicago, Ill, USA). Normally distributed data will be reported as mean  $\pm$  standard deviation (SD). If the distribution of data do not follow the Normal distribution, median and interquartile range will be reported. An intent-to-treat analysis will be performed at 2 time points (end of the treatment period [day 42] and one month later [day 72]). The proportions of complete healing, clinical improvement, and withdrawal will be compared between the two groups by calculating Absolute

Risk Reductions (ARR) based on the proportion of complete healing, which is defined as more than 75% reduction in the size of the lesion compared with baseline in each group. Ninety-five percent confidence intervals (95% CIs) will be provided. To compare the mean for data with normal distribution one-way analysis of variance (ANOVA) and for data that do not follow normal distribution proper nonparametric statistical tests were used. Fisher exact test was used to compare the rates of relapse and drug-related adverse events. A 2-sided  $P < 0.05$  will be considered significant.

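### Mean time to heal is a secondary objective in the summary only, and the protocol's one rule for comparing means does not suit an outcome that is unobserved for unhealed or lost lesions

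*Protocol*

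**What the plan says.** The protocol lists its secondary objectives twice, and the lists differ.

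- *Secondary objectives* in the opening summary has three comparisons: relapse, "the mean time to heal of the lesions", and adverse effects.
- *Secondary objectives* under *Goal and Objectives* has two: "the proportion of relapsed patients 6 months after initiation of treatment", and adverse effects. Time to heal is absent.
- *Outcome measures* agrees with the shorter list: "The secondary end-points include treatment related side effects and relapse".

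*Statistical methods* has one general rule for means. It begins "To compare the mean for data with normal distribution one-way analysis of variance (ANOVA" and continues "for data that do not follow normal distribution proper nonparametric statistical tests were used". It does not mention time to heal, censoring or any survival method.

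*Sample size* sets the expected healing rates: "Fifty-six lesions per treatment group were needed to have 80% power to detect a significant difference in the expected cure rate of 60" per cent with the injection alone, against "the desired cure rate of 85" per cent with a dressing, "at week 10 with a type I error level of 0.05". It also allows for 20% loss to follow-up. Visits are weekly during the six weeks of treatment, then about a month later (day 72 in *Statistical methods*), then on day 180.

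**The concern.** The two lists cannot both be right. Read from the summary, time to heal is a planned comparison. Read from the main text, it is not an end point and has no definition or assessment rule.

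If it is an objective, the general rule for means is the only method on offer. ANOVA needs a number for every lesion, but a lesion that is unhealed or lost when observation stops has no healing time. An analyst would then have to leave such lesions out or give them an arbitrary value. Leaving them out compares subsets selected on the outcome after randomisation. The arm that heals more lesions also brings more of its slow healers into its average, so its advantage shrinks.

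The visit schedule adds to the difficulty. A healing time after day 42 is known only to within 72 − 42 = 30 days, and one after day 72 only to within 180 − 72 = 108 days.

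**Working it through.** **The plan's own figure.** For 60% against 85%, two-sided 5% and 80% power, the two-proportion formula gives 57 per group with continuity correction and 49 without. The stated 56 is therefore reproduced to within one, which confirms 60% and 85% as the design rates.

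**Share without a healing time at week 10.** Control: 1 − 0.60 = 40%. Dressing: 1 − 0.85 = 15%. Losses come on top.

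**Size of the attenuation if only healed lesions are averaged.** The protocol gives no healing-time distribution, so an exponential one is assumed, matched to the two rates at week 10.

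- Hazard: λ = −ln(1 − p)/10, giving 0.0916 and 0.1897 per week (ratio 2.07).
- Mean among lesions healed by week 10: 1/λ − 10(1 − p)/p.
  - Control: 10.91 − 6.67 = 4.25 weeks.
  - Dressing: 5.27 − 1.76 = 3.51 weeks.
- Restricted mean to week 10 over all lesions: p/λ.
  - Control: 0.60 × 10.91 = 6.55 weeks.
  - Dressing: 0.85 × 5.27 = 4.48 weeks.

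The same formulas with 26 in place of 10 (day 180 is about week 26), and p equal to the share healed by then, give the second row.

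| Cut-off | Unhealed, control / dressing | Healed-only difference | Restricted-mean difference | Ratio |
|---|---|---|---|---|
| Week 10 | 40% / 15% | 0.7 weeks | 2.1 weeks | 0.36 |
| Week 26 | 9% / 1% | 3.2 weeks | 4.7 weeks | 0.68 |

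**Effect on power to week 10.** Two arms of 56 independent lesions were simulated 4,000 times per model, with visits at weeks 1 to 6 and 10 and no losses.

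| Assumed healing pattern | Healed-only ANOVA | Healed-only rank test | Rank test, unhealed ranked last | Log-rank |
|---|---|---|---|---|
| Exponential | 20% | 20% | 86% | 90% |
| Weibull, shape 2 | 18% | 18% | 86% | 88% |
| Dressing changes whether, not when, a lesion heals | 5% | 5% | 65% | 75% |

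The direction is the same under all three models. The power is lost by leaving unhealed lesions out. A rank test that keeps them recovers most of it.

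**The case against.** A reader might infer that the protocol plans to drop unhealed lesions. It does not say so. The rule for means is generic, is never tied to time to heal by name, and could be meant for other measurements such as lesion size. The unnamed nonparametric tests could include a log-rank test, or a rank test that keeps unhealed lesions. An intent-to-treat analysis is announced, although for two fixed time points. All of this stands, so the attenuation is conditional.

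A second objection is that censoring rules are commonly left to a statistical analysis plan, which is not at hand. That is fair for the detail. It does not remove the disagreement between the protocol's own lists, nor the poor fit of the only rule the protocol states.

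Third, a reader might take the one-third figure as the size of the problem. It depends on stopping at week 10, a limit the summary does not set for time to heal. By week 26 the ratio is about two thirds. *Background* says that almost all lesions heal within several months even untreated, so most week-10 failures are late healers.

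Fourth, one could give each unhealed lesion the last visit time. With no losses this reproduces the restricted mean. With 20% loss it does not, because a lesion lost at week 2 would count as a fast healer.

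Finally, it would be too strong to say that the trial hides the dressing's benefit. The proportion healed is the primary comparison, reported as a risk difference with confidence intervals. Only this secondary comparison is exposed.

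**Conclusion.** The point holds in two parts. The inconsistency is certain and needs no assumption: time to heal is an objective in the summary and absent from both main-text sections. The mismatch of method also stands, because the only stated rule for means makes no provision for the 40% and 15% of lesions expected to be uncured at week 10, or for the losses.

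The attenuation follows only if that rule is applied to healed lesions alone, which the documents do not state. In that case the healed-only difference would be between about one third (week 10) and two thirds (week 26) of the restricted-mean difference. These ratios rest on the exponential assumption and on the 60% and 85% rates. They also set two different estimands side by side, so they show scale rather than a bias in one estimate. If the objective is deleted, the analysis question falls away.

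**What to change.** Reconcile the summary with *Goal and Objectives* and *Outcome measures*, either by deleting time to heal from the summary or by adding it to both main-text sections.

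If it is kept, add to *Statistical methods*:

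- Time to heal runs to the first visit with more than 75% reduction in lesion size from baseline, the protocol's own definition of complete healing.
- It is analysed in all randomised patients, with unhealed and lost lesions censored.
- The method is Kaplan-Meier with a log-rank test or, closest to the stated interest in a mean, the restricted mean to day 72. It should allow for the gaps between visits and for several lesions per patient, since up to five are permitted.
- This replaces ANOVA or a rank test on healed lesions.

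The cost is a few sentences and a little more analysis work. No new data are needed, because lesion size is already recorded at each visit. Censoring lost lesions assumes that loss is unrelated to healing, and the text should say so.

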## **Eligibility criteria**

Eligible patients will be treated by administration of either intralesional injections of meglumine antimoniate (Glucantime®; Rhodia Laboratories, Rhone-Poulenc, France) alone, or a combination of intralesional injections of meglumine antimoniate injections with application of a dressing (Atrauman ,®Hartmann, CMC Consumer Medical Care GmbH, Germany) or a combination of intralesional injections of meglumine antimoniate injections with application of a silver containing dressing (Atrauman® Ag ,Hartmann, CMC Consumer Medical Care GmbH, Germany) on the lesions. The dressing will be applied on the lesions and will remain there for a week .Totally ,this study is expected to be conducted in 12 months. Six weeks of interventions and 6 months follow-up from the first visit of each patient is planned. The patients will be visited at weekly intervals and the characteristics of their lesions will be recorded on the Case Report Forms (CRFs) . After the 7th visit ,the patients will be visited one month later and the last visit will be on the day 180.

**Keywords:** *Leishmania major*, cutaneous leishmaniasis, dressing

## Background

Cutaneous leishmaniasis (CL) is a major health problem in many developing countries and affects hundreds of thousands of people each year. It is associated with a high disease burden at both individual and social levels in endemic areas. Looking for simple, inexpensive treatment methods is continued. Unfortunately the conventional treatments of CL tend to concentrate only on the treatment of the microbial cause of this disease and little attention have been paid to other aspects of wound management in this disease. For example although as a rule all chronic wounds are colonized to some degrees with different microorganisms and it is well known that when the bacterial burden of the wound gradually increases, it could interfere with normal wound healing and deteriorate the inflammation and pain of the wound, in the majority of randomized clinical trials that have assessed the efficacy of different therapeutic interventions for acute OWCL, principles of wound management has been ignored. As it has been previously mentioned in literature review, using silver dressings might assist healing of the CL lesions through several mechanisms. This study is designed to assess of the efficacy of a combination of intralesional (i. l.) injections of meglumine antimoniate (MA) and silver dressing in comparison with the intralesional injections of MA in the treatment of CL due to *L. major* through conducting a randomized, assessor-blind controlled clinical trial

Leishmaniasis is caused by different species of intracellular protozoan *Leishmania* and transmitted by the bite of infected sand flies [1]. Leishmaniasis is endemic in 88 countries, mostly developing ones [4]. Ninety percent of all CL cases occurs in only 7 countries; Afghanistan, Algeria, Brazil, Iran, Peru, Saudi Arabia and Syria [5]. Iran is endemic for CL. Almost all CL cases are caused by either *L. tropica* or *L. major*. CL has been reported from all provinces and is endemic in many of them. In some villages surrounding Kashan, cumulative

incidence of CL was estimated to be around 13.1 % in 1996 [6]. CL due to *L. major* usually manifests as appearance of a papule or small nodule at the site of parasite inoculation 1 to 2 months after the sand fly bite. Over a period of several weeks, the lesion will develop into an ulcer with moderate occasionally hemorrhagic exudate and crust which is accompanied by induration of the peri-ulcer skin. The skin at the periphery of the lesion is usually erythematous. In almost all cases the lesion will heal with scarring over a period of several months even in absence of treatment [1-3]. The active lesion and remaining scar can be associated with a high burden on different aspects of patient's life [11]. Many treatment modalities have been used in the treatment of CL, but, pentavalent antimonials are considered as the first line drugs for treatment of CL so far. They have to be administered only as intramuscular, intravenous or intralesional injections and could be associated with severe side effects and significant discomfort [12]. There is no vaccine available for prevention of CL for general human use [13]. A recently published systematic review demonstrated that no effective, safe and inexpensive treatment is currently available for CL [12]. It is logical to imagine that bringing all aspects of wound management paradigm into consideration for treating ulcerative lesions of CL may improve the results of any intervention that are used in the treatment of CL cases. Wound management paradigm includes treating the cause, wound bed preparation and patient related concerns. Wound bed preparation contains debridement, control of inflammation or infection and moisture balance [14]. Unfortunately the conventional treatments of CL tend to concentrate only on the treatment of the microbial cause of this disease and little attention have been paid to other aspects of wound management in this disease. In the majority of randomized clinical trials that have assessed the efficacy of different therapeutic interventions for AOWCL, principles of wound management has been ignored [12]. Silver exerts its antimicrobial effects through several

mechanisms. The main mechanism is thought to be the interaction with DNA and inhibiting reproduction and cell division [17, 18]. Silver also can disrupt the bacterial cell wall by interacting with bacterial enzymes and proteins which are important for cell respiration and nutrients transportation [17, 19]. Silver with a positive charge (cationic silver) has antimicrobial activity [19]. All silver based dressings achieve their antimicrobial effects by releasing cationic silver ( $\text{Ag}^+$ ). Cationic silver binds to thiol groups and alters the normal function of proteins and leads to bacterial cell wall rupture. Bacterial cell death will occur as a result of leakage of the cell contents. Also silver ion can bind to bacterial enzymes and interfere with cell respiration and nutrient transportation [19]. Navarro et al. [22] noted that the anti-leishmanial effect of these silver complexes is related to interaction with parasitic DNA [22]. A further mechanism by which silver may enhance wound healing in CL lesions is its reported anti-inflammatory effects. Silver may reduce the activity of matrix metalloproteinase (MMP), which has been linked with delayed wound healing and inflammation [17, 21].

## **Goal and Objectives**

Primary objective: To compare the proportion of cured patients between treatment group treated with intralesional (i.l.) injections of meglumine antimoniate (MA) (and non-silver dressing and treatment group treated with intralesional (i.l.) injections of meglumine antimoniate (MA) 10 and 14 weeks of follow-up . To compare the proportion of cured patients between treatment group treated with intralesional (i.l.) injections of meglumine antimoniate (MA) and silver dressing and treatment group treated with intralesional (i.l.) injections of meglumine antimoniate (MA) 10 and 14 weeks of follow-up.

## **Secondary objectives**

### **To compare:**

- the proportion of relapsed patients 6 months after initiation of treatment
- the proportion of adverse effects during the study period in three groups

### **To answer:**

- Is the combination of intralesional (i.l.) injections of meglumine antimoniate (MA) and non-silver dressing more effective than the intralesional injections of MA in the treatment of CL due to *Leshmania major*?
- Is the combination of intralesional (i.l.) injections of meglumine antimoniate (MA) and silver dressing more effective than the intralesional injections of MA in the treatment of CL due to *L. major*

## **Patients and Methods**

### **Design and setting**

This study is designed as a three parallel arm with 1:1:1 allocation ratio randomized, assessor-blind clinical trial and will be conducted in Kashan where is endemic for CL due to *L. major*.

Kashan is located about 210 km south of Tehran, capital of Iran.

### **Inclusion criteria**

- a) Parasitologically confirmed cases of CL based on positive smear and/or culture
- b) Otherwise healthy subjects on the basis of medical history
- c) Age of 12 to 60 years
- d) Willingness to participate in the study and signing the informed consent form (by the patient or his/her parent/guardian in cases younger than 18 years).

**Exclusion criteria**

- a) Pregnant or lactating women
- b) Duration of lesion more than 3 months
- c) Number of lesions more than 5
- d) Ulcer size greater than 5 cm in largest diameter
- e) History of receiving full course standard treatment (antimonials)
- f) History of allergy to meglumine antimoniate (MA) or silver
- g) Serious systemic illnesses (as judged by the physician)
- h) Participation in any drug trials in the last 60 days
- i) Indication for systemic treatment with MA
- j) Presence of secondary bacterial infection of the lesion according to clinical appearance.

**Withdrawal criteria**

- a) Occurrence of a serious adverse event, or
- b) Withdrawal of the consent

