### **Follow up**

An assessor who is blinded to the type of treatment will visit the patients at weekly intervals during the treatment period and 1-month and 5 months after the last treatment session. The patients will receive their dressings from the members of the study team other than the assessors and will be instructed to take off their dressings before each visit and not to explain to assessors whether they have used dressing or not.

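### A serious adverse event is a withdrawal criterion beside withdrawn consent, so patients who still consent may go unmeasured; say that it ends treatment only and that scheduled visits continue

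*Protocol*

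**What the plan says.** The Withdrawal criteria section of the protocol consists of two alternatives, "Occurrence of a serious adverse event, or" and withdrawn consent. The first is not limited by cause or relation to treatment. The section does not say what the patient is withdrawn from.

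Four other places bear on the question:

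- **Follow up.** A blinded assessor "will visit the patients at weekly intervals during the treatment period and 1-month and 5 months after the last treatment session". Patients who stop treatment early are not mentioned.
- **Summary part, under its Eligibility criteria heading.** Six weeks of intervention and six months of follow-up, counted from the first visit, are planned for each patient. A visit one month after the seventh visit and a last visit on day 180 are named. Withdrawn patients are not mentioned.
- **Statistical methods.** "An intent-to-treat analysis will be performed at 2 time points", namely day 42 and day 72. The same section adds: "The proportions of complete healing, clinical improvement, and withdrawal will be compared between the two groups".
- **Outcome measures.** Relapse is "assessed 5 months after the termination of treatment".

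**The concern.** Withdrawn consent normally ends participation. When a serious adverse event stands beside it without distinction, study staff may treat the two alike and stop seeing a patient who would still attend. Comparing withdrawal as a proportion alongside complete healing and clinical improvement supports that reading, since it makes withdrawal look like a final status.

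What is at stake depends on when the event occurs:

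- Before day 42: both cure assessments could be lost.
- Between day 42 and day 72: the day 72 assessment could be lost.
- After day 72: only the relapse assessment and any further adverse events could be lost. The serious event itself is already known.

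Such loss may be related to treatment or outcome. Whether a visit takes place is trial conduct, so it belongs in the protocol. A statistical analysis plan can say how a missing value is handled but cannot supply the measurement. Comparing withdrawal between groups would show the loss without repairing it.

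**Working it through.** **1. The plan's own figure.** Sample size gives 56 lesions per group for 60% against 85%, 80% power and type I error 0.05; Statistical methods gives a two-sided test. With mean proportion 0.725:

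- Uncorrected n = [1.96 × √(2 × 0.725 × 0.275) + 0.8416 × √(0.60 × 0.40 + 0.85 × 0.15)]² / 0.25² = (1.2377 + 0.5102)² / 0.0625 = 48.9, so 49.
- With continuity correction: (48.9 / 4) × [1 + √(1 + 4 / (48.9 × 0.25))]² = 56.6, so 57 against the stated 56. The figure reproduces.
- Allowance for 20% loss: 56 × 1.2 = 67.2, so 68; 56 / 0.8 = 70. The protocol settles on this: "recruiting 68 (round up to 70) lesions per treatment group will be reasonable".

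The point does not change the sample size. The figure of 70 is the denominator used below.

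**2. Size per affected patient.** The exclusion "Number of lesions more than 5" means that a patient contributes between one and five lesions. Keep all 70 lesions in the denominator and let k lesions be unmeasured. The arm's cure proportion then lies between (c + 0)/70 and (c + k)/70, where c is the number of measured lesions that are cured. The width is k/70, whatever the arm or cure rate.

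| Unmeasured lesions (k) | Width, k/70 | Share of the 25-point planned difference (85 − 60) |
|---|---|---|
| 1 | 1.4 points | 1.4 / 25 = 6% |
| 5 | 7.1 points | 7.1 / 25 = 29% |

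These are bounds for one patient, not expected effects. The second row needs a patient with the maximum number of lesions, all unmeasured, compared between all cured and none cured.

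**3. The milder reading.** Suppose withdrawal means only stopping injections and dressing. The Follow up section still ties weekly visits to the treatment period and later visits to the last session. Take the protocol's day 42 as the end of treatment and day 72 as one month later, and consider a patient stopped at day 14. Counted from that patient's own last session, both later visits move forward by 42 − 14 = 28 days. The one-month visit falls at day 72 − 28 = 44, and no visit is assured at day 72. The schedule in the summary, counted from the first visit, would keep days 42, 72 and 180. The two sections therefore give staff no single rule for a patient who stops early.

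**The case against.** The strongest case against is that this is silence rather than error. The protocol nowhere says that follow-up ends after a serious event. The summary separates intervention from follow-up, counts follow-up from the first visit and applies it to each patient, which favours continued measurement. Intent-to-treat analysis is already planned, withdrawal is compared between groups, and 20% loss is allowed for.

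Part of this stands. The text is ambiguous, and the summary's schedule is real evidence for the milder reading. The intent-to-treat plan also makes a further clause about analysis in the randomised arm unnecessary. But the summary does not say that its schedule survives withdrawal, and the milder reading still leaves day 72 unassured for a patient stopped early. The loss allowance protects the number of lesions, not against loss related to outcome.

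A reader might infer three stronger things that the documents do not support:

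- **That the protocol orders follow-up to stop.** It does not; it permits that reading.
- **That power is in danger.** With 70 lesions per group, no other loss and withdrawn lesions counted as not cured (normal approximation, no continuity correction), power is 92.1% with none withdrawn. It is 90.0% if 2% are withdrawn in both arms, and 55.5% if 10% are withdrawn in the dressing arm only. These rates are assumptions. The protocol gives no serious event rate, and nothing in it suggests 10% in one arm.
- **That a serious event should no longer stop treatment automatically.** Treatment stops under either reading, and nothing here argues for replacing that safety rule with discretion.

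**Conclusion.** The point holds as a cheap improvement. The withdrawal rule can be applied so that patients who still consent are not measured at the planned intent-to-treat time points or for relapse, and no section rules this out.

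The expected effect is probably very small. Participants are "Otherwise healthy subjects on the basis of medical history", serious systemic illness is excluded, and no serious event rate is given from which an expected loss could be worked out. The range of 1.4 to 7.1 points is a bound per affected patient. It assumes 70 lesions in the arm, all kept in the denominator. Confidence is medium, because the text can be read either way.

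**What to change.** Two small edits:

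- **Withdrawal criteria.** Keep the stop of study treatment after a serious adverse event, and state that it ends treatment only. Withdrawn consent remains the ground for ending participation.
- **Follow up.** State that, after treatment has stopped, lesion measurement and adverse event recording continue at the originally scheduled visits unless the patient withdraws consent. Count these from the first visit: weekly through day 42, then day 72 and day 180.

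The cost is a sentence in one section and a clause in the other. The visits are already planned, and the sample size and analysis do not change. The downside is some effort to obtain visits from patients who have stopped treatment.
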